### Sample Size

This study will aim to recruit 180 patients to participate in the study and come for clinical assessments. A formal power calculation for the sample size was not conducted as this project was funded as a feasibility study. Therefore, sample size estimates are not required.

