### Setting and Site Selection

The National Institute for Health Research (NIHR) Clinical Research Network North West London will contact research active practices with the goal of setting up to 14 general practices for research across North West London. Research active practices are defined as practices with a previous record of carrying out research activities.

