### Participant Enrollment

To participate in the study, potentially eligible patients will be identified from the general practice databases by administrative staff at each participating general practice using automated eligibility search pertaining to prescribed medication. To maximize recruitment, patients will be invited by post, SMS text messaging, and opportunistically. General practices using post and text invitations will invite patients to come to prescheduled appointments. Practices inviting patients opportunistically will invite patients as part of routine clinical care. Patients will be invited in the order of acceptance until 180 patients come into their first visit.

Patients invited by post will be mailed study materials (invitation and patient information sheet) by general practice administrative staff. Opportunistically recruited patients will be invited by their health care professionals and receive study materials in paper copy. Finally, patients invited by SMS text messaging on their mobile phones by general practice administrative staff will receive study materials electronically. Patients who decide not to participate will be given an option to complete an anonymous sociodemographic survey either in paper copy with a prepaid envelope (if invited by post or opportunistically) or using a weblink to a Web-based Qualtrics survey (if invited by SMS text messaging). There will be no financial incentives for study participation.

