### Data Collection

The sociodemographic survey containing information on comorbidities (stroke, heart disease, hypertension, familial hypercholesterolemia, kidney disease, type 2 diabetes, and dementia), age, gender, ethnicity, education, partial postcode, and smartphone ownership will be collected among study participants through the Web app. In addition, sociodemographic data (not including smartphone ownership or education) for study participants will be obtained from their medical records by general practices. Among consenting nonparticipants, the sociodemographic survey will be administered anonymously (with no possibility of further data linkage) either using a paper or a Web-based survey. All potentially eligible patients will not be asked to respond to the sociodemographic survey. Instead, anonymous sociodemographic data will be obtained from these patients’ medical records by general practices. The number of invited individuals will be recorded by the general practice staff. Medication adherence at weeks 1, 12, and 24 will be collected from secondary data.

During the baseline visit, health care professionals will set up participants to use the Web app from their work computer with the internet using a prespecified Web address on a clinician interface of the Web app. During 20-minute consultations at weeks 1, 12, and 24, a health care professional will take and input clinical measurements (blood pressure, height, weight, smoking, and nonfasting cholesterol) into the clinician interface of the Web app (see Multimedia Appendix 1).

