The acceptability of the Cholesterol CarePlan will be assessed using patients’ readiness to embrace new technologies, the usability of the Web app, and patient satisfaction. Patients’ behavior in relation to readiness to adopt new technology will be examined using the 12-item TRI [30]. The Web app usability will be assessed using the 10-item SUS [31]. Furthermore, patient satisfaction with the Cholesterol CarePlan will be assessed using a questionnaire developed by the AHA.

The efficacy of the Cholesterol CarePlan will be judged by examining the Web app compliance with changes in medication adherence and clinical risk factors. Medication adherence will be collected from secondary data using the Medication Possession Ratio and Proportion of Days Covered. These measures are based on the number of days medication supplied and the quantity of medication dispensed for each filled prescription [34,35]. A difference-in-difference (DID) analysis using multiple linear regression, controlling for education, socioeconomic deprivation, ethnicity, gender, and age will be performed. Using DID, a time-series average change in medication adherence, cholesterol, smoking, blood pressure, and body mass index over 3 time-points will be compared among full compliers and partial compliers, respectively, with Web app noncompliers. Interactions in regression models will be explored using explanatory variables. In addition, subgroups analyses (by education, socioeconomic deprivation, ethnicity, gender, and age) will explore differences in medication adherence and clinical outcomes among full compliers, partial compliers, and noncompliers with the Web app. Finally, using multiple regression modeling while controlling for education, socioeconomic deprivation, ethnicity, gender and age, average changes in diet, physical exercise, and quality of life will be examined among Web app compliers.

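### The efficacy models leave out general practice, so practice-specific changes that track app compliance can pass for an app effect and P values ignore clustering

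*Protocol article*

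**What the plan says.** Under Statistical Analysis, the Protocol article plans a DID by multiple linear regression, "controlling for education, socioeconomic deprivation, ethnicity, gender, and age will be performed". It compares full and partial compliers with noncompliers over three time-points. The outcomes are medication adherence, cholesterol, smoking, blood pressure and body mass index. A second regression, of change in diet, exercise and quality of life among compliers only, names the same five covariates, and the subgroup list repeats them. No practice term, random effect, clustered standard error or invitation-route covariate is named. Significance is judged at P<.05 without multiplicity adjustment.

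Other sections show how much runs through the practice:

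- Setting and Site Selection gives the goal of "setting up to 14 general practices for research across North West London".
- Participant Enrollment describes the route by practice: "General practices using post and text invitations will invite patients to come to prescheduled appointments", whereas "Practices inviting patients opportunistically will invite patients as part of routine clinical care".
- Data Collection says that at the baseline visit "health care professionals will set up participants to use the Web app from their work computer". A health care professional also takes blood pressure, height, weight, smoking status and nonfasting cholesterol at weeks 1, 12 and 24.

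The sample size is a target without a power basis: "This study will aim to recruit 180 patients to participate in the study and come for clinical assessments" and "A formal power calculation for the sample size was not conducted as this project was funded as a feasibility study".

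**The concern.** A practice can influence app compliance through whom it invites, by which route, and how well it sets patients up. It can also influence change in the outcomes, through changes in lipid or blood pressure care during the study or through drift in measurement. None of the five patient covariates represents this. If practices where patients use the app more are also those where risk factors improve more, compliers will appear to do better than noncompliers even with no app effect. Separately, patients from one practice are not independent, and the stated models treat them as if they were.

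The Discussion says that once effects are established, the team will seek funding for a randomized trial. A signal produced by practices could feed into that decision.

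**Working it through.** The protocol states no effect size, standard deviation, intraclass correlation (ICC) or power, so there is no figure to reproduce. The document inputs are 180 patients, up to 14 practices and P<.05 (taken as two-sided). All variance and correlation inputs below are assumptions, shown as ranges.

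**1. Patients per practice.** m = 180/14 = 12.86.

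**2. Clustering without bias.** Compliance varies within practice, so an approximate design effect for the compliance contrast is DE = 1 + (m − 1) × ρx × ρy. Here ρx is the ICC of compliance and ρy the ICC of change. The true type I error is 2 × [1 − Φ(1.96/√DE)].

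| ρx | ρy | DE | True error |
|---|---|---|---|
| 0 | any | 1.00 | 5.0% |
| 0.1 | 0.05 | 1 + 11.86 × 0.005 = 1.06 | 5.7% |
| 0.3 | 0.05 | 1 + 11.86 × 0.015 = 1.18 | 7.1% |
| 0.3 | 0.10 | 1 + 11.86 × 0.030 = 1.36 | 9.2% |

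**3. Clustering in the compliers-only model.** An average change among compliers takes the full design effect, 1 + (m − 1) × ICC. Assume 8.6 to 12.9 compliers per practice.
- ICC 0.02, m = 8.6: DE = 1 + 7.6 × 0.02 = 1.15, true error about 7%.
- ICC 0.05, m = 12.9: DE = 1 + 11.9 × 0.05 = 1.59, true error about 12%.

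**4. Bias, in SD units.** Simulation with no app effect: 180 patients, 14 practices, half compliers, SD of change 1, 2,000 runs per setting, compliance ICC 0.1 and 0.3. Least squares was fitted to change scores, with and without practice indicators.

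| Practice effects | Bias without practice (SD) | False positives without practice |
|---|---|---|
| Level only | about 0 | about 5% |
| Change ICC 0.02-0.10, correlation 0 with compliance | 0 | 4-9% |
| Change ICC 0.02-0.05, correlation 0.5 | 0.04-0.10 | 6-12% |
| Change ICC 0.10, correlation 0.5 | 0.08-0.14 | 9-17% |
| Change ICC 0.02-0.10, correlation 1 (extreme) | 0.07-0.26 | 8-43% |

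With practice indicators, bias was about 0 and false positives about 4-6% throughout.

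**5. Bias, on the cholesterol scale.** A second simulation used 14 × 13 patients, a patient SD of change of 0.7 mmol/L, an SD of 1 between practices in the log-odds of compliance, and a practice SD of change of 0.1-0.2 mmol/L. The implied ICC runs from 0.01/(0.01 + 0.49) = 0.02 to 0.04/(0.04 + 0.49) = 0.075. At correlation 0.5 the spurious difference is 0.04-0.08 mmol/L with 7-12% false positives. At correlation 0.8 it is 0.06-0.12 mmol/L with 10-22%. With practice in the change model, bias is about 0 and false positives 5-6%.

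**6. Which practice term works.** With complete follow-up, the compliance-by-time coefficient in a DID fitted to levels equals mean change in compliers minus mean change in noncompliers. A practice effect that is constant over time adds the same amount at every visit and drops out of each patient's change, so including it leaves the coefficient unaltered. Simulation agrees. With a practice SD of change of 0.15 and correlation 0.5, bias is 0.064 mmol/L without and 0.064 with a time-invariant practice effect; at correlation 0.8 both are 0.094. The bias goes only when practice is allowed to differ in change.

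**The case against.** The strongest objection is that the DID already deals with most of what a reader would fear. A reader might infer that any difference between practices is read as an app effect. The documents do not support that. Case mix, device or operator offsets and other stable differences cancel. Bias needs three things together: practices differing in compliance, practices differing in change, and the two going together. The documents give no figure for any of them. This stands, and it limits the point to what can happen.

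A reader might also infer that the practice measures every outcome. It does not. Medication possession and days covered come from secondary prescribing data. The MARS, SF-12, diet, exercise and persistence are self-reported. Measurement drift at the practice therefore bears only on the clinical measures, although practice-level changes in care could still affect the others. Nor does the protocol say who chooses the invitation route, only that it differs by practice.

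Patient self-selection into compliance is probably the larger bias, and a practice term does not remove it. Where practice drives compliance but not change, conditioning on practice can slightly amplify it: 0.15 to 0.18 under one set of assumed inputs. The simulations in steps 4 and 5 contain no self-selection, so their near-zero bias with practice included does not describe the whole study. This stands too.

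Finally, efficacy is a secondary objective of a feasibility study, and a fuller analysis plan might handle practice. The secondary status caps the importance. It does not remove the point, because the article states the adjustment set explicitly, gives the same set for both models, and leaves out a feature of its own design.

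**Conclusion.** The point holds in a limited form. The stated efficacy models omit practice and make no allowance for clustering, although practice structures recruitment, app set-up and clinical measurement. Practice-specific change that goes with practice-level compliance can be mistaken for an app effect. At an assumed correlation of 0.5 and modest ICCs, false positives are about 6-12% against a nominal 5%, with a spurious cholesterol difference of about 0.04-0.08 mmol/L. If practice change is unrelated to compliance, there is no bias and only the P values are affected. The size rests wholly on assumed inputs. The change is worth making because it is cheap, but it would not turn a comparison of self-selected compliers and noncompliers into a causal estimate.

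**What to change.** In the analysis plan:

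- Keep a practice code in the transferred data. Data Handling and Security says the host deidentifies app data before transfer, and the article does not show whether practice survives that step.
- Add practice-by-time effects to the DID, or practice effects to a change-score model. A time-invariant practice effect alone is not enough (step 6).
- In the compliers-only model, allow for clustering by practice with a small-sample correction, since 14 clusters are few.
- Report results with and without the practice terms.
- Tabulate recruitment, dropout and app compliance by practice. This also serves the primary feasibility objective.

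The cost is a few sentences, a retained code and up to 13 degrees of freedom (14 − 1) per change contrast. Practices with few or no noncompliers will add little to the within-practice comparison, which may be common with about 13 patients per practice. Self-selection remains and may be slightly amplified, so efficacy estimates should still be presented as exploratory.

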### Ethical Considerations

Prior to being awarded the funding grant, the study underwent AHA’s internal medical review examining its medical importance, design, quality, and safety reporting. In addition, the study underwent external peer review, received favorable ethics opinion from the North of Scotland Research Ethics Committee, Health Research Authority approval, and was adopted onto the NIHR Clinical Research Network portfolio.

## Results

This study is currently funded by the American Heart Association. Initial study recruitment will take place between February and July 2018 followed by patient follow-up. Patient level data will be obtained in January 2019. Data analysis will be completed by February 2019. Results will be submitted for publication in March 2019.

## Discussion

To the best of our knowledge, this is the first study examining the feasibility and acceptability of administering AHA’s Cholesterol CarePlan as a Web app to patients. The benefits to patients of using the AHA Cholesterol CarePlan may be improved medication adherence, changes to diet, physical exercise, clinical risk factors, and quality of life. The benefits to the scientific community include an understanding of whether the Web app may be successfully taken up by patients and whether it may help improve lifestyle and management of cholesterol. The benefits to health services may be the delivery of more effective CVD prevention programs.

Although patients treated for hyperlipidemia with cholesterol- lowering drugs will be aware of their CVD risk and the need for cholesterol-lowering medication, as well as lifestyle changes, they may not adhere to medication, engage in a regular physical activity, or consume a healthy diet, all of which are needed for successful cholesterol management. The action and maintenance of behavioral change may require ongoing motivational support. The maintenance of behavioral change in relation to medication adherence and lifestyle is important for controlling cholesterol and preventing the premature onset of CVD [12,14,36]. To change patients’ behavior to prevent the premature onset of CVD, according to the Health Belief Model, patients must perceive themselves to be at increased risk of CVD, perceive the severity of illness, and weigh the barriers to behavioral change against the benefits thereof [37]. An important factor for controlling cholesterol, according to the Transtheoretical Model, is the maintenance of behavioral change in relation to medication adherence and lifestyle [38].

Persuasive technology using convincing and effective communication is theorized to help change behavior in relation to CVD. This technology is modeled on ideas that behaviors change only when people are motivated, able and have appropriate triggers [22]. Interventions delivered through smartphones may improve medication adherence [36]. Given the high level of penetration of smartphones among people of lower socioeconomic status, there is an opportunity for health-related mobile apps to overcome traditional barriers to CVD prevention. Nonetheless, a possible limitation of using smartphones for the prevention of CVD is the existence of the digital divide with lower socioeconomic groups retaining older technologies. An important barrier to app use is privacy concerns in relation to data sharing and personal safety. Despite observed associations between app use and positive behavioral change, there is limited evidence on the sustainability of behavioral change using apps [22].

A possible methodological threat to study design may be in selection bias with more wealthy patients owning a smartphone being able to participate in the study; we will be able to assess to what extent those who take part in our study represent the wider eligible population. Another possible limitation may be the use of self-reported questionnaires. However, the use of biometric assessments and medication prescribing may cross-validate the self-reported medication compliance. As this is a feasibility study, no sample size calculations were required. Once study effects are established, the aim is to apply for further funding to design a randomized controlled trial with fully specified sample size criteria.

## Appendix

Multimedia Appendix 1 Data collected by the Web app.

Multimedia Appendix 2 Patient pathway.

Multimedia Appendix 3 The timeline of quantified assessments recorded through the Web app.

Multimedia Appendix 4 Data flow diagram.

## Abbreviations

AHA: American Heart Association
CVD: cardiovascular disease
DHM: Digital Healthcare Management
DID: difference-in-difference
ICL: Imperial College London
MARS: Medication Adherence Rating Scale
NHS: National Health Service
NIHR: National Institute for Health Research
N3: the trusted broadband network for NHS healthcare
SF-12: Short-Form Health Survey
SMS: short message services
SUS: System Usability Scale
TRI: Technology Readiness Index
